## Results

This study has been funded by the National Medical Research Council of Singapore in November 2016 and approved by domain-specific review board of the National Health Group in April 2016.

Data were collected from November 2016 to present (as of submission date of manuscript). Numbers recruited into study, as of submission of the manuscript, were 140. The status of data analysis and expected results are expected to be published in the years 2023-2024, when the information is available.

## Discussion

### Study Findings

This is the largest prospective clinical study on the use of IOCS in MSTS from a variety of primary malignancies. It will provide significant clinical evidence regarding the safety and applicability of IOCS in MSTS. The clinical safety of the use of IOCS has been established in oncological surgical procedures involving gastrointestinal [40], gynecological [41-43], hepatobiliary [40,44-46,55-57], and urological [47-54,58-62] specialties (Multimedia Appendix 1). However, the use of IOCS has neither been studied nor practiced regularly in metastatic musculoskeletal tumor surgeries (MMTSs). This may be because of the skepticism among surgeons about the safety of SBT in MMTSs, despite the presence of substantial supporting evidence in other surgical specialties in the field of oncology [40-54,63,64]. Amidst all the apprehension regarding IOCS, a retrospective comparative review has shown that SBT indeed reduces the need for postoperative ABT [69]. More recently, the use of SBT has been studied prospectively, demonstrating its safety for IOCS in MSTS [70]. Nonetheless, these studies did not have a comparative arm and had a small sample size.

This prospective clinical study is founded on substantiating evidence that salvaged blood is free from viable tumor cells, proven in our earlier methodical basic sciences approach [32,38]. We aim to study the OS, as well as tumor progression in MSTS patients through analysis of their various outcome measures. The results from this approach will help debunk the prevailing myth that IOCS contributes to disease progression either in the form of new metastasis or in the form of an increase in the size of the index lesion.

### Limitations

The limitation of this study is that not all patients undergoing MSTS will survive for the total follow-up period of 4 years, thereby theoretically leading to potential underreporting of disease progression. The sheer number of possible primary tumors in MSD also inevitably leads to heterogeneity, which can be overcome through propensity score–matching analysis.

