## Methods

### Recruitment

This study aims to recruit a minimum of 90 patients of whom 30 will receive SBT (with or with no allogeneic blood), 30 will undergo ABT, and the remaining 30 will have NBT. From our experience of treating patients with tumor, there are likely to be very few patients who receive only SBT. The majority of patients receiving SBT are likely to receive both SBT and ABT in various proportions. SBT and ABT form the 2 experimental arms, whereas patients with NBT form the control cohort. We will compare the number of patients receiving only SBT with those receiving ABT, if the sample sizes are sufficient.

Patients will be selected from specialist outpatient spine clinics or inpatient wards. These patients may be referred from an inpatient medical oncology team for management, especially in the setting of MSD with cord compression resulting in symptoms such as pain or neurology. A thorough examination of clinical history, physical examination, and review of imaging will be done, and appropriate patient management options will be discussed by the attending orthopedic surgeon. During the enrollment period, whenever a spine surgeon has obtained surgical consent for MSTS in patients with MSD, the principal investigator (NK) will be informed either by a telephone call or by text messaging.

The *research assistant* who is on-site at the National University Hospital during office hours or any member of the research team who is available will interview the patient. During this interview, the interviewer will confirm whether the inclusion criteria are fully met. The study will be explained to suitable subjects, including the advantages as well as possible intra- and postoperative risks of the reinfusion of salvaged blood. A copy of the *patient information sheet and consent form* will be provided to the patient, detailing the recruitment procedures, our objectives, hypotheses, and background information, and any queries will be addressed. Subsequently, written informed consent will be obtained from the patient.

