Blood transfusion details will be collected from anesthetists immediately after the operation. Depending on the type of blood transfusion done during the surgery, that is, ABT only or SBT with or with no ABT or NBT, the patient will be categorized into the appropriate study cohort. All patients undergoing MSTS will receive tranexamic acid as an intravenous bolus before induction of anesthesia as per the department protocol, with subsequent top-up dosages every 4 hours during MSTS. If excessive blood loss is expected during surgery, such as in a separation surgery, continuous infusion of tranexamic acid is given to the patient.

Postoperatively, all subjects will be followed up individually by their operating surgeons, as per the standard of care at the National University Hospital. No additional patient follow-up sessions by the research team will be required. Clinical data and patient outcomes will be accessed via the computerized patient support system and EPIC system at monthly intervals. All available radiological data and clinical notes from the patients’ follow-up by their treating surgeons or physicians will be reviewed by the research team. This is to determine the postoperative outcomes such as survival and disease progression. The collected data will be analyzed postoperatively at 3, 6, 12, 24, 36, and 48 months. The data collection and follow-up of available records will continue over a period of 4 years postoperatively or until the patient’s demise, whichever occurs first. The collected outcomes of the 2 experimental groups (patients who received SBT with or without ABT) will be compared with those of the control group (patients who received NBT) as well as with the available historical data from the literature.

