### Statistical Analysis

We have defined *disease progression* as the increase in the size of an existing metastatic lesion or the appearance of a new lesion in the lung, liver, or the spinal column, which can be visualized by using radiological imaging.

Demographic and clinical characteristics of patients will be summarized using mean (SD) values for continuous variables with approximately normal distribution, median (IQR) values for continuous variables with skewed distribution, and frequency (percentage) for categorical variables. A 1-way ANOVA will be used to compare the mean of a normally distributed variable across the 3 blood transfusion groups, whereas a Kruskal-Wallis rank test will be used for the comparison of medians. A Fisher exact test will be implemented for categorical variables accounting for potential small frequencies.

The association between individual characteristics and OS will be studied by using the Kaplan-Meier curve and a log-rank test. The crude hazard ratio and its 95% CI will be used to measure the association between individual characteristics and OS and will be calculated based on their original definitions. Multivariate Cox proportional hazard regression will then be used to adjust for statistically significant confounders for the relationship between the type of blood transfusion and OS. The proportional hazards assumption will be tested after the final model is obtained.

The association between the type of blood transfusion and tumor progression will be investigated by the competing risks analysis, taking death without tumor progression as the competing event. First, cumulative incidence curves of the 3 blood transfusion groups will be plotted nonparametrically, and then we will model the relation via a subdistribution hazard regression model. The measure of association will be quantified by the crude subdistribution hazard ratio; its 95% CI and *P* value will be analyzed in a univariate analysis. Subsequently, a multivariate analysis will be used to adjust for potential confounders. All statistical analyses will be done using Stata Special Edition 14.0 (StataCorp LP). The statistical tests will be assumed to be 2-sided, with the conventional 5% significance level.

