#### Analysis of Secondary Outcome Measures

The progression of disease will be assessed using the internationally accepted Response Evaluation Criteria in Solid Tumors (version 1.1) [66,67]. Disease progression is defined as at least a 20% increase in the sum of the diameters of measurable target lesions (eg, lymph nodes and bone metastases with soft tissue components), unequivocal progression of nontarget lesions (eg, malignant ascites or pleural effusions), or the appearance of 1 or more new metastatic lesions.

Computed tomography of chest or abdomen and pelvis will be used to assess metastases in the lymph nodes, lung, liver, or any abdominal organ, all of which can be visualized adequately. Magnetic resonance imaging of whole spine and nuclear medicine bone will also be performed because of their increased sensitivity in detecting early new spinal or skeletal metastases [68]. A lesion identified in a follow-up study in an anatomical location that is not present at baseline is considered a new lesion and will indicate disease progression.

The OS rate will be defined as the proportion of patients who survive until the end of the study period. Median survival times and 95% CI will be estimated using Kaplan-Meier curves for experimental and control groups. The median OS times will be compared using a log-rank test. The survival rate at 6 months after surgery will also be estimated using Kaplan-Meier curves.

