### Broader Implications

Through the reporting of our analysis, this study will help reduce the use of ABT, reduce the burden on blood banks, and improve the overall blood management of patients with MSTS. This improvement in blood management will prevail even with the improvement of surgical techniques in the management of MSTS, that is, introduction of minimally invasive surgery techniques and the regular use of navigation. This is because the 2 techniques mentioned earlier will reduce blood loss during the steps of spinal instrumentation but are unlikely to have any effect on blood loss while performing decompression. Decompression and separation surgery presently still form a major component of MSTS and will continue to do so, resulting in significant bleeding that requires replenishment potentially in the form of SBT.

In this protocol, we have proposed a prospective observational nonrandomized study design as the ethical appropriateness of blinding or randomizing these patients is a key concern in our region and country. Blinding or randomization of patients with MSD could be deemed unethical, especially among patients who may not agree to receive SBT or ABT as this will limit the blood transfusion type applicable for them. This could be attributed to the current lack of clinical evidence that SBT does not lead to disease progression or shortened survival among patients undergoing MSTS who receive SBT. With this research proposal, we aim to highlight the safety profile of SBT, together with a design protocol applicable for use in patients with MSD. Future research, such as propensity-matched studies, can be done to further validate the outcomes from our current protocol.

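### The log-rank test of overall survival pools all primary tumours, and the remedy the article names for their heterogeneity is not in its own analysis

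*Protocol article*

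**What the plan says.** - **Heterogeneity and its remedy (Limitations).** "The sheer number of possible primary tumors in MSD also inevitably leads to heterogeneity, which can be overcome through propensity score–matching analysis".
- **Where matching is placed (Broader Implications).** "Future research, such as propensity-matched studies, can be done to further validate the outcomes from our current protocol". The Statistical Analysis section and its two subsections on outcome measures name no propensity method.
- **Between-group OS test (Analysis of Secondary Outcome Measures).** "The median OS times will be compared using a log-rank test". No stratification factor is given.
- **Adjusted OS analysis (Statistical Analysis).** "Multivariate Cox proportional hazard regression will then be used to adjust for statistically significant confounders for the relationship between the type of blood transfusion and" (the outcome named there is overall survival). Primary tumour is not named.
- **Adjusted progression analysis (Statistical Analysis).** A multivariable subdistribution hazard model is planned, adjusting for potential confounders that are not named.
- **Design.** The study is observational and non-randomised (Broader Implications). Patients are assigned to a cohort after the operation, by the transfusion they received (Recruitment). OS is one of the primary objectives, and the hypothesis is that salvaged blood does not increase risk.

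**The concern.** Primary tumour type can be a strong predictor of survival, and the article itself treats the range of primaries as a limitation. Leaving such a factor out of a survival comparison has two separate effects.

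1. **Attenuation.** Even when the tumour mix is the same in each group, pooling strata with different hazards pulls the hazard ratio (HR) towards 1 and costs power. Poor-prognosis patients die early, and they do so faster in the group at higher risk, so the survivors being compared become less alike over time.
2. **Confounding.** When the mix differs between groups, the crude HR is shifted in whichever direction the mix favours.

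The study hopes to conclude that there is no increased risk, so a test with little sensitivity to harm is a weak basis for that conclusion. Matching would deal with the second effect only. It does not by itself restore power lost to heterogeneity of outcome, and it discards unmatched patients from groups of about 30.

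**Working it through.** **Inputs from the article.** Testing: "The statistical tests will be assumed to be 2-sided, with the conventional 5% significance level". Size: "This study aims to recruit a minimum of 90 patients of whom 30 will receive SBT", with 30 in each of the other two groups; 30 + 30 + 30 = 90 agrees. Recruitment: "Numbers recruited into study, as of submission of the manuscript, were 140", so 140/3 ≈ 47 per group if equal. Follow-up runs "over a period of 4 years postoperatively or until the patient’s demise, whichever occurs first". No power, effect size, event count or margin is stated, so there is no power figure to reproduce.

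**Ceiling without heterogeneity.** For 1:1 groups, Schoenfeld power is Φ(√d × ln HR / 2 − 1.96). If all 60 patients in a 30 versus 30 comparison die and HR = 2.0, then √60 × 0.693 / 2 − 1.96 = 0.72, which gives 77%. For HR = 1.5 the power is 35%. Events needed for 80% power are 4 × (1.96 + 0.84)² / (ln HR)²: 66 for HR 2.0 and 191 for HR 1.5.

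**Assumptions not in the article.** Exponential survival; three equally common tumour strata; a median of 12 months in the middle stratum; stratum hazard multipliers as in the table; censoring at 48 months; 30 versus 30; 3000 runs per scenario (simulation error at most about 1 point). HR above 1 means harm from salvaged blood.

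**Balanced tumour mix, crude versus stratified log-rank power**

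| Multipliers | Crude HR (true 2.0) | Power, HR 2.0 | Power, HR 1.5 |
|---|---|---|---|
| 0.7 / 1 / 1.4 (mild) | 1.94 | 69% vs 68% | 30% vs 30% |
| 0.4 / 1 / 2.5 (moderate) | 1.71 | 50% vs 66% | 21% vs 29% |
| 0.25 / 1 / 4 (strong) | 1.52 | 33% vs 64% | 15% vs 28% |

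The stratified HR is about 2.02 throughout when the truth is 2.0. With 46 per group and moderate spread, power at HR 2.0 is 65% crude and 86% stratified. A separate simulation with assumed stratum medians of 4/10/24 and 3/10/30 months gave 53% vs 70% and 41% vs 66% at 30 per group.

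**Uneven mix, moderate spread.** Let the salvaged-blood group be 22/33/45% good/middle/poor prognosis and the comparison group 45/33/22%. The mean starting multipliers are:

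- salvaged blood: 0.22 × 0.4 + 0.33 × 1 + 0.45 × 2.5 = 1.543
- comparison: 0.45 × 0.4 + 0.33 × 1 + 0.22 × 2.5 = 1.060

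Their ratio is 1.46 at time zero with no true effect. Over full follow-up the simulation gives:

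| Mix in salvaged-blood group | True HR | Crude HR | Harm declared, crude test |
|---|---|---|---|
| Worse | 1.0 | 1.39 | 22% |
| Worse | 2.0 | 2.37 | 87% |
| Better | 1.0 | 0.71 | 0.1% |
| Better | 2.0 | 1.22 | 12% |

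With the better mix and true HR 2.0, the stratified test has 63% power. With true HR 1.0, the stratified test rejects in about 5% of runs under either mix.

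**Would the planned Cox model pick up tumour type?** The significance rule was read as a 5% log-rank screen of tumour group. With wide spreads (medians 4/10/24 or 3/10/30), a three-level grouping passes in 99 to 100% of runs. With mild spread (6/10/16) it passes in 88% of runs at 90 patients and 97% at 141. A 12-level ungrouped factor with mild heterogeneity passes in only about 68% at 90 patients.

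**Cost of matching.** If matching left 20 per group, stratified power at HR 2.0 with moderate spread would fall from about 64 to 66% to 48%.

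**The case against.** The strongest reply is that the treatment effect on OS is not left crude. The article plans a multivariable Cox model, and where tumour type matters most the significance screen would almost always select it. Where the screen might miss it, heterogeneity is mild and little power is at stake. That is largely right, and it narrows the point. A reader who saw only the log-rank sentence might infer that OS is never adjusted; the Statistical Analysis section shows otherwise. What remains is that selection is not certain, particularly for a factor with many ungrouped levels. A mild factor that is unevenly distributed can still confound, and the log-rank result will be reported crude whatever the Cox model contains.

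A second reply is that covariate lists and strata are commonly left to the statistical analysis plan. That holds for the lists. The point here is about what the article does state: a test with no stratum, a significance rule for choosing Cox covariates, and a remedy that another section assigns to other studies.

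A third reply is that Limitations only says matching can overcome heterogeneity, which can be read together with a later study. That is fair: the article does not promise matching in this study. It does leave the reader unsure how this study handles the problem.

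Finally, stratification and covariate adjustment are both accepted methods, and three strata by three groups at 90 patients is about 10 per cell. Either method meets the point.

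**Conclusion.** The point holds in a limited form. The stated log-rank comparison of OS ignores a factor that the article calls an inevitable source of heterogeneity. The remedy it names lies outside its own analysis. Adjustment through the Cox model is likely but not assured.

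With a balanced mix and true HR 2.0, the crude test costs about 0 points of power (mild spread), 16 (moderate) or 31 (strong). A reader might infer that the crude analysis always pulls a real harm towards no difference and so favours the hoped-for answer. The documents do not support that: it requires a balanced mix, and cohorts formed by the transfusion received give no assurance of one. With an uneven mix the crude result can hide harm, exaggerate it or create it.

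All sizes depend on the assumed survival, tumour mix and effect, and on two-group comparisons. The article supplies none of these figures. Stratifying also does not rescue the study's size: the ceiling for HR 2.0 at 30 versus 30 is 77%.

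**What to change.** 1. Define a small number of primary-tumour prognosis groups, for example three, and date the definition before outcomes are examined. Outcome data are already being collected, so the grouping should be set without reference to them.
2. In Analysis of Secondary Outcome Measures, stratify the log-rank test by these groups.
3. In Statistical Analysis, include the same factor in the Cox model (as stratum or covariate) and in the subdistribution model, whatever its significance.
4. Report the adjusted OS result as the main one and the crude result as supportive.
5. Reconcile Limitations with Broader Implications: state that propensity matching is not part of this study and that heterogeneity is handled by the stratified or adjusted analysis.

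The cost is analysis wording only, assuming that primary tumour is in the clinical record. Recruitment and follow-up do not change. The downside is that the grouping must be fixed in advance and small strata add little information. If prognosis differs little between primaries, the gain in power is close to nil, but little is lost (about 1 point in the mild scenario).

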### Broader Implications

Through the reporting of our analysis, this study will help reduce the use of ABT, reduce the burden on blood banks, and improve the overall blood management of patients with MSTS. This improvement in blood management will prevail even with the improvement of surgical techniques in the management of MSTS, that is, introduction of minimally invasive surgery techniques and the regular use of navigation. This is because the 2 techniques mentioned earlier will reduce blood loss during the steps of spinal instrumentation but are unlikely to have any effect on blood loss while performing decompression. Decompression and separation surgery presently still form a major component of MSTS and will continue to do so, resulting in significant bleeding that requires replenishment potentially in the form of SBT.

In this protocol, we have proposed a prospective observational nonrandomized study design as the ethical appropriateness of blinding or randomizing these patients is a key concern in our region and country. Blinding or randomization of patients with MSD could be deemed unethical, especially among patients who may not agree to receive SBT or ABT as this will limit the blood transfusion type applicable for them. This could be attributed to the current lack of clinical evidence that SBT does not lead to disease progression or shortened survival among patients undergoing MSTS who receive SBT. With this research proposal, we aim to highlight the safety profile of SBT, together with a design protocol applicable for use in patients with MSD. Future research, such as propensity-matched studies, can be done to further validate the outcomes from our current protocol.

### Conclusions

We surmise that the results of our proposed study design will pave the way for future randomized studies on the use of IOCS in MSTS and MMTSs, given that the granting bodies and their reviewers would be more open to considering funding for such studies.

## Appendix

Multimedia Appendix 1 Key papers evaluating the use of intraoperative cell salvage in various cancer surgeries.

## Abbreviations

ABT: allogeneic blood transfusion
CTC: circulating tumor cell
IOCS: intraoperative cell salvage
LDF: leukocyte depletion filter
MMTS: metastatic musculoskeletal tumor surgery
MSD: metastatic spine disease
MSTS: metastatic spine tumor surgery
NBT: no blood transfusion
OS: overall survival
SBT: salvaged blood transfusion
